#### Calculation rationale

2.5.1

The sample size was determined based on the primary outcome (AUC comparison between model-assisted and clinician-only diagnoses) using a two-group superiority design. Key parameters were derived from prior studies on AI diagnostic tools (31, 32):

Expected effect size: ΔAUC = 0.15 (clinically meaningful improvement).

Type I error (*α*): 0.05 (two-tailed).

Power (1-*β*): 0.95.

Attrition rate: 20% adjustment for patient dropout or incomplete data.

The minimum sample size for AUC comparison was calculated using the following formula (33):

$$n=\frac{{\left(Z_{1-\alpha /2}+Z_{1-\beta }\right)}^{2}\times [\mathrm{AU}C_{1}(1-\mathrm{AU}C_{1})+\mathrm{AU}C_{2}(1-\mathrm{AU}C_{2})]}{{\left(\mathrm{AU}C_{1}-\mathrm{AU}C_{2}\right)}^{2}}$$

Where:

$\mathrm{AU}C_{1}$
 (model-assisted): 0.85 (34).

$\mathrm{AU}C_{2}$
 (clinician-only): 0.70 (null hypothesis).

$Z_{1-\alpha /2}$
= 1.96, 
$Z_{1-\beta }$
= 1.645.

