#### Sample size derivation

2.5.2

The sample size calculation began with an initial estimate of 145 patients per group (290 total), derived from a power analysis targeting a clinically significant ΔAUC of 0.15 (*α* = 0.05, *β* = 0.95). To account for potential 20% attrition due to incomplete data or participant dropout, the final patient sample was adjusted to 174 per group (348 total). For clinicians, a minimum of 218 participants (109 per group) was required to ensure balanced representation across experience levels (resident, attending, chief) while addressing hospital-level clustering effects, as recommended by methodology for cluster-randomized trials (35). This dual-tiered approach balances statistical precision with pragmatic considerations, ensuring robust evaluation of the AI model’s impact in diverse clinical environments.

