#### Final allocation

2.5.3

The study will enroll a total of 348 patients, comprising both retrospective cohorts (historical data from 2019 to 2024) and prospective cohorts (real-time data from the 2025 influenza season). Clinician participation includes 218 practitioners, stratified by hospital tier (urban vs. rural) and seniority level (resident, attending, or chief physician) to ensure balanced representation of clinical expertise and institutional resource variability. This allocation strategy optimizes statistical power while reflecting real-world healthcare diversity, supporting robust validation of the AI model across heterogeneous settings.

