#### Justification

2.5.4

The patient sample size was determined through a power analysis to ensure ≥80% statistical power for detecting a clinically meaningful improvement (ΔAUC more than 0.15) in diagnostic accuracy, aligning with FDA guidelines for validating AI-driven medical devices (36).

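### The 20% attrition allowance is multiplied on rather than divided out, so 174 per group covers only a 16.7% loss; the effect on power is small

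*Protocol article*

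**What the plan says.** Section 2.5.1 (Calculation rationale) lists among its key parameters "Attrition rate: 20% adjustment for patient dropout or incomplete data". The others are a two-sided type I error of 0.05, power of 0.95, and AUCs of 0.85 (model-assisted) and 0.70 (clinician-only), a difference of 0.15. It also prints the sample size formula.

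Section 2.5.2 (Sample size derivation) begins with "an initial estimate of 145 patients per group (290 total"). It then explains the next step: "To account for potential 20% attrition due to incomplete data or participant dropout", "the final patient sample was adjusted to 174 per group (348 total"). The inflation formula is not written out.

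Section 2.5.3 (Final allocation) carries the result forward: "The study will enroll a total of 348 patients".

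Section 2.5.4 (Justification) gives a second power target. It says the patient number was chosen "to ensure ≥80% statistical power for detecting a clinically meaningful improvement".

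**The concern.** A base number, a loss rate and an enrolment number are all printed, and they do not fit together. If 20% of enrolled patients are lost, enrolment must be the base divided by 0.80. Adding 20% of the base gives a smaller number and leaves fewer evaluable patients than the base, whatever the base is.

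The stake is whether the enrolment figure of 348 does what the text says it does. A second stake is that the same method would be carried over if the base number were later corrected.

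**Working it through.** **Inputs.** Base 145 per group, final 174 per group (section 2.5.2); attrition 20% (sections 2.5.1 and 2.5.2); total 348 (section 2.5.3); AUCs 0.85 and 0.70, Z values 1.96 and 1.645 (section 2.5.1).

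**1. Reproducing the plan's figure.** 145 x (1 + 0.20) = 174.0, and 2 x 174 = 348. This matches exactly, so the allowance was multiplied on.

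**2. What 174 leaves.** 174 x (1 - 0.20) = 139.2, so 139 per group. In total 348 x 0.80 = 278.4, so 278 against the 290 set. The shortfall is about 6 per group, or 4% of 145.

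**3. What loss 174 tolerates.** 1 - 145/174 = 0.167, so 16.7%.

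**4. What dividing would give.** 145/(1 - 0.20) = 181.25, rounded up to 182 per group (364 total), 16 more than 348.

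**5. Power by the printed formula.** The variance term is 0.85 x 0.15 + 0.70 x 0.30 = 0.1275 + 0.2100 = 0.3375. Divided by 0.15² = 0.0225, this is 15. The formula is therefore n = 15 x (Z sum)², and solved for power it is Phi(√(n/15) - 1.96).

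| Evaluable per group | √(n/15) | Power |
|---|---|---|
| 139 (174 less 20%) | 3.044 | 86.1% |
| 145 (the stated base) | 3.109 | 87.5% |
| 174 (no loss at all) | 3.406 | 92.6% |

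The inflation step costs about 1.4 percentage points.

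**6. The base number.** With the printed inputs, n = 15 x (1.96 + 1.645)² = 15 x 12.996 = 194.9, so 195 per group. The figure of 145 does not follow. For 80% power the same formula gives 118, and for 90% it gives 158.

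**7. If 145 had been right for 95% power.** Scaling the Z sum gives Phi(3.605 x √(139.2/145) - 1.96) = Phi(1.572) = 94.2%, a loss of about 0.8 points.

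**8. Carrying the method to a corrected base.** 195 x 1.2 = 234, which leaves 187 after 20% loss and about 94.2% power. 195/0.80 = 243.75, so 244 per group, which keeps 195.

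**The case against.** *A 20% adjustment might mean a plain 20% top-up.* The wording in section 2.5.1 allows this, but the item is labelled as an attrition rate and section 2.5.2 says the step accounts for 20% attrition. If a top-up was meant, the claim that it covers a 20% loss is still wrong as written. This objection does not stand.

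*The effect is trivial.* This largely stands. The slip costs about 1 point of power on either basis, and 139 per group is still above the 118 that 80% power needs. It does not make the printed numbers consistent.

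*Real losses may be below 20%.* Section 2.2.2 excludes patients with incomplete baseline data, sections 2.4.4, 2.7.4 and 2.8.4 plan imputation, and section 2.5.3 counts retrospective records among the 348, where dropout in the usual sense hardly applies. This stands as a caution that 139 is what follows from the plan's assumption, not a forecast. The plan itself chose 20%.

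*The base number is the larger error, so this point is moot.* The first half stands. The second does not: if the base is corrected and the multiplication kept, the new number falls short of its target in the same way (step 8).

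**Conclusion.** The enrolment figure is wrong as written: 174 per group does not preserve 145 under the 20% attrition the plan assumes. It leaves 139, and it covers a loss of 16.7%.

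A reader might infer that this slip makes the trial miss its stated power. The documents do not support that. They state two powers. The 80% of section 2.5.4 is met at 139 per group (86.1%). The 0.95 of section 2.5.1 is missed at 139, at 145, and even at 174 with no loss, because the base is 145 where the printed formula gives 195. The attrition step adds little to that gap.

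A reader might also infer that enrolling 182 per group settles the matter. It would restore 145 evaluable patients and with them only 87.5% power.

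The head-counts in steps 1 to 4 need no assumption beyond reading 20% as the share lost. The power figures take the protocol's formula and AUCs as printed. Whether that formula suits a design with clustered readers is a separate question.

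**What to change.** Reword sections 2.5.2 and 2.5.3 in one of two ways:

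- 174 per group (348 total) allows for 16.7% attrition; or
- at 20% attrition, 174 per group leaves 139 evaluable per group, with about 86% power by the printed formula.

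Either is a one-sentence change and needs no extra patients.

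Separately, reconcile the base number with the printed formula, and the 0.95 of section 2.5.1 with the 80% floor of section 2.5.4. When that is done, apply n/(1 - 0.20) to the corrected base. If 95% power and the printed inputs are kept, this gives 244 per group (488 total, 140 more than 348), not 234; that cost belongs to correcting the base as well as the inflation. Changing to 182 per group (16 more patients) as a stand-alone repair is not advised, since it keeps the unsupported 145.

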#### Phase IV: randomized controlled trial

2.3.4

This phase is a pragmatic randomised controlled design to assess the effectiveness of AI-assisted diagnosis in the real world. Clinicians will be assigned in a 1:1 ratio to either the control group (using standard clinical assessment protocols) or the AI model-assisted group. Allocation will be by block group randomisation, stratified by hospital level (urban vs. rural) and clinician experience level (resident, attending, chief) to ensure balanced representation in key subgroups.

The control group will rely exclusively on routine diagnostic workflows, while the model-assisted group will integrate AI outputs into their decision-making process and retain full authority to accept or reject recommendations. The primary outcome is the between-group AUC difference, with a ΔAUC greater than 0.15 defined as clinically significant, which is consistent with the U.S. Food and Drug Administration’s (FDA) benchmarks for diagnostic tools based on artificial intelligence or machine learning (AI/ML). The design simulates real-world clinical practice and quantifies the added value of AI in improving diagnostic accuracy while preserving clinician autonomy.

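### Section 2.5.2 says clustering is addressed through the clinician number, but the patient number that carries the power has no allowance for patients nested in randomised clinicians

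*Protocol article*

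**What the plan says.** Section 2.3.4 (Phase IV) makes the clinician the unit of allocation: "Clinicians will be assigned in a 1:1 ratio to either the control group" or to the AI-assisted group. Section 2.6.1 stratifies by urban or rural tier and by clinician experience. The individual hospital is neither randomised nor a stratum.

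Section 2.5.1 introduces its one equation with "The minimum sample size for AUC comparison was calculated using the following formula (33"). The inputs are a type I error of "0.05 (two-tailed"), "Power (1-*β*): 0.95", and AUCs of 0.85 and 0.70.

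Section 2.5.2 reports 145 patients per group, raised to 174 (348 in total) for 20% attrition. It then gives 218 clinicians, 109 per group, for balance across experience levels "while addressing hospital-level clustering effects, as recommended by methodology for cluster-randomized trials (35").

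Section 2.5.3 describes the 348 as a mix of retrospective (2019 to 2024) and prospective (2025) patients. Section 2.5.4 says the patient number was chosen "to ensure ≥80% statistical power for detecting a clinically meaningful improvement".

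**The concern.** When clinicians are randomised and each assesses one or more patients, the diagnoses made by one clinician tend to resemble each other. A sample size for independent patients then overstates the information in the data. Section 2.5.2 tells the reader that this has been dealt with, yet nothing in the displayed patient calculation deals with it. The level it names, the hospital, is also not the level that the Phase IV allocation creates, which is the clinician.

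At stake is a stated property of the design. The power is presented as allowing for clustering when the number behind it does not. The cost grows if some clinicians contribute many more patients than others, and the article neither excludes nor quantifies that.

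**Working it through.** **Inputs from the article.** Two-sided alpha 0.05 (z = 1.96); power 0.95 (z = 1.645); AUCs 0.85 and 0.70; 145 then 174 patients per group; 20% attrition; 218 clinicians.

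**Inputs not in the article (assumed).** Clinician-level correlation ρ from 0.05 to 0.30; coefficient of variation (CV) of patients per clinician, 0 or 1; all evaluable patients belong to Phase IV and each is assessed by one clinician.

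**Step 1: the plan's own figure.** The formula is n = (1.96 + 1.645)² × [0.85 × 0.15 + 0.70 × 0.30] / 0.15².
- The bracket is 0.1275 + 0.2100 = 0.3375, and 0.3375 / 0.0225 = 15.
- So n = 12.996 × 15 = 194.9, or 195 per group. The printed 145 does not reproduce.
- Inverting the formula, power = Φ(√(n/15) − 1.96). For n = 145 this is Φ(3.109 − 1.96) = 87.5%.

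The starting point for judging clustering is therefore 87.5%, not 95%.

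**Step 2: is there room for a design effect?** 174/145 = 1.20 exactly. Attrition accounts for the whole step, and the formula before it has no cluster size, correlation or reader variance. No allowance for clustering is stated anywhere between the inputs and 174.

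**Step 3: what clustering would cost.** I use 145 evaluable per group, as the plan intends after attrition. (A full 20% loss from 174 would leave 139; that is a separate matter.)
- Mean patients per clinician: m = 290/218 = 1.33.
- Design effect: DE = 1 + [(1 + CV²)m − 1]ρ.
- Effective patients per group: 145/DE, put into the power formula of step 1.

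| CV | ρ | DE | Effective n per group | Power |
|---|---|---|---|---|
| – | 0 | 1.00 | 145 | 87.5% |
| 0 | 0.05 | 1.017 | 142.6 | 86.9% |
| 0 | 0.30 | 1.099 | 131.9 | 84.3% |
| 1 | 0.05 | 1.083 | 133.9 | 84.8% |
| 1 | 0.30 | 1.498 | 96.8 | 71.9% |

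For the last row: 1 + (2 × 1.330 − 1) × 0.30 = 1.498; 145/1.498 = 96.8; Φ(√(96.8/15) − 1.96) = Φ(0.580) = 71.9%.

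**Step 4: margin against 80%.** By the same formula 80% power needs about 117.7 patients per group, so 145 tolerates a design effect up to 145/117.7 = 1.23. Equal clusters stay below that over the whole assumed range. With CV = 1 the limit is passed when 1.66ρ exceeds 0.23, that is at ρ of about 0.14.

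**The case against.** **The analysis handles it.** Sections 2.4.1 and 2.8.1 plan the Dorfman-Berbaum-Metz (DBM) multi-reader method, which allows for differences between clinicians. That is true of the analysis, but DBM does not enter the sample size. It does bear on the repair: under a multi-reader design the variance has reader, case and reader-by-case parts, so the simple design effect above may not be the right form.

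**The derivation of 218 may exist elsewhere.** The article is condensed and cites a method for this number. This stands in part. The text does not show how 218 was obtained, so one cannot say that no clustering calculation lies behind it. What can be said is that none is shown for 218 and none enters the patient number, whose derivation is displayed. Hospital-level correlation can also exist when hospitals are not randomised, so naming it is not wrong in itself.

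**The clusters are small.** This stands for equal clusters: the loss is then about 1 to 3 percentage points, and power stays above the 80% of section 2.5.4.

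**A stronger reading to avoid.** A reader might infer that clustering takes the power from 95% to about 75%. With 348/218 = 1.6 patients per clinician, CV = 1 and ρ = 0.30, the 174 per group act as about 105, and the formula gives 75%. The documents do not support that comparison. By the same formula 174 independent patients give only 92.6%, so part of the gap is the arithmetic error. The figure counts enrolled rather than evaluable patients, and it combines the upper ends of two assumed ranges. Nor does any section say that a few busy clinicians will supply most patients; uneven accrual is plausible but not documented.

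**Conclusion.** The point holds in a limited form. Section 2.5.2 says that clustering is addressed, but the patient number contains no allowance for it, and the number of clinicians cannot supply one.

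Under the stated assumptions, clustering by clinician lowers the power from 87.5% to between 87% and 84% with equal clusters, and to between 85% and 72% with a CV of 1. The correlation, the CV and the mean of 1.33 are all assumptions. The mean is especially uncertain because section 2.5.3 mixes retrospective and prospective patients without a split by phase. The fall from 95% to 87.5% belongs to the separate discrepancy between 145 and 195. The point should be corrected because a stated design property is unsupported, although the loss is modest at low correlations and equal cluster sizes.

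**What to change.** 1. In section 2.5.2, delete the statement that 218 clinicians address clustering, or support it with the calculation.
2. State the assumed mean number of Phase IV patients per clinician (m), its CV, and the clinician-level correlation ρ.
3. Divide the evaluable patients per group by 1 + [(1 + CV²)m − 1]ρ, or use a multi-reader variance consistent with the planned DBM analysis.
4. Restate the resulting power in sections 2.5.1, 2.5.2 and 2.5.4, which at present give "Power (1-*β*): 0.95", "α* = 0.05, *β* = 0.95" and at least 80% respectively.

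No cap on patients per clinician is needed. A low cap would restrict accrual in a phase described as pragmatic. It would also sit badly with the DBM analysis, since a clinician's own AUC needs at least one severe and one non-severe case.

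The cost is one short calculation and a few sentences. The stated power becomes somewhat lower.

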#### Final allocation

2.5.3

The study will enroll a total of 348 patients, comprising both retrospective cohorts (historical data from 2019 to 2024) and prospective cohorts (real-time data from the 2025 influenza season). Clinician participation includes 218 practitioners, stratified by hospital tier (urban vs. rural) and seniority level (resident, attending, or chief physician) to ensure balanced representation of clinical expertise and institutional resource variability. This allocation strategy optimizes statistical power while reflecting real-world healthcare diversity, supporting robust validation of the AI model across heterogeneous settings.

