#### Hospital inclusion criteria

2.1.1

We have pre-set criteria for hospital eligibility for the study. Hospitals must be accredited tertiary general hospitals, which provide full emergency and inpatient services. Hospitals should have at least 100 patients with influenza diagnosed by laboratory testing between 2021 and 2023. Hospital clinicians must use electronic health records (EHRs) so that symptoms of influenza patients and other information used for clinical research can be recorded in a standardised format. Longitudinal, anonymous data sharing programmes must be in place within hospitals to ensure the security of patient and clinician information.

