#### Phase V: prospective validation study

2.3.5

As Dai et al. illustrate the point, using prospective cohort data validation provides a better view of the model’s performance in the real world (24). This final phase evaluates the model’s real-world clinical utility during the 2025 influenza season. The AI model will be deployed in real time to analyze EHRs of newly admitted influenza patients across all 87 hospitals. Clinicians will receive model-generated predictions (such as risk scores, key contributing factors) within 2 h of case entry via a secure, institution-specific dashboard.

Data collection will capture:

Clinician actions: Initial diagnosis (pre-model assessment), final diagnosis (post-model review), and time-to-decision (minutes from case entry to diagnosis).Model performance: Concordance between model predictions and ground truth (severe influenza confirmed by an independent adjudication panel).

This prospective design validates the model’s operational feasibility, diagnostic timeliness, and accuracy in dynamic clinical environments, providing critical evidence for scalability and regulatory approval.

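### The 348 patients sized for the two-arm AUC comparison are also declared the whole study's total, so any retrospective patient counted in them leaves Phase IV below its own computed size.

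*Protocol article*

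**What the plan says.** Section 2.5.1 (Calculation rationale) sets up a two-group superiority comparison of AUC between model-assisted and clinician-only diagnosis, with "Power (1-*β*): 0.95". Section 2.5.2 (Sample size derivation) reports 145 per group, allows for 20% attrition, and concludes that "the final patient sample was adjusted to 174 per group (348 total". Section 2.3.4 makes the between-group AUC difference the primary outcome of Phase IV, the randomised phase.

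Section 2.5.3 (Final allocation) states: "The study will enroll a total of 348 patients, comprising both retrospective cohorts (historical data from 2019 to 2024) and prospective cohorts".

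Section 2.7.2 (Data collection timeline) assigns Phases I and II to retrospective data and Phases III to V to prospective data from the 2025 season.

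Other parts of the article describe much larger data sources. Section 2.3.1 draws model-development records from 87 hospitals over 2019 to 2024. For Phase V, section 2.3.5 says: "The AI model will be deployed in real time to analyze EHRs of newly admitted influenza patients across all 87 hospitals".

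Section 2.5.4 (Justification) gives a second power target, namely "to ensure ≥80% statistical power for detecting a clinically meaningful improvement".

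**The concern.** Two arms of 174 use up all 348 patients. If the same 348 must also contain 2019 to 2024 records, and Phase IV can use only prospective patients, the arms cannot both reach 174. Phases III and V are prospective as well, so they may draw on the same remainder.

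At stake is the number on which the confirmatory comparison rests. Section 2.5.3 is the article's only statement of total patient enrolment. Followed to the letter, it either leaves Phase IV short by an unknown amount or puts records from the model-development period into the trial of that model. In both cases a reader cannot tell which phase the power statement describes.

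**Working it through.** **Inputs (sections 2.5.1 and 2.5.2).** AUC 0.85 model-assisted and 0.70 clinician-only; difference 0.15; two-sided alpha 0.05 (z = 1.96); power 0.95 (z = 1.645); attrition 20%; 145 per group before attrition and 174 after.

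**Reproducing the plan's figure.** The formula in section 2.5.1 is

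n = (z_alpha + z_beta)² × [AUC1(1 − AUC1) + AUC2(1 − AUC2)] / (AUC1 − AUC2)²

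- Variance term: 0.85 × 0.15 + 0.70 × 0.30 = 0.3375.
- Divided by 0.15² = 0.0225, this is 15.
- (1.96 + 1.645)² = 12.996, so n = 12.996 × 15 = 194.9, or 195 per group.

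The stated 145 is not reproduced. It corresponds to about 87.5% power, which the article states nowhere. The step to 174 is 145 × 1.20, and 2 × 174 = 348.

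**The allocation conflict.** This part does not depend on whether 145 is right.

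1. Section 2.5.2: 348 = 174 + 174, all in one two-group comparison.
2. Section 2.3.4: that comparison is the Phase IV primary outcome.
3. Section 2.7.2: Phase IV is prospective.
4. Section 2.5.3: the 348 include retrospective patients.

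From these, the Phase IV total is 348 minus the retrospective patients, minus any prospective patients used only in Phases III or V. It equals 348 only if both deductions are zero, and section 2.5.3 says the first is not.

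**What a shortfall does to power.** The share f of the 348 that is in Phase IV is not given, so it is an assumption and is shown as a range. With n = 174f per arm, the plan's formula gives power = Φ(√(n/15) − 1.96). For f = 1: √(174/15) = 3.406, less 1.96 is 1.446, and Φ = 0.926.

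| Share in Phase IV | n per arm | Power | n per arm after 20% loss | Power |
|---|---|---|---|---|
| 100% | 174 | 92.6% | 139.2 | 86.1% |
| 90% | 156.6 | 89.8% | 125.3 | 82.4% |
| 75% | 130.5 | 83.9% | 104.4 | 75.1% |
| 50% | 87 | 67.3% | 69.6 | 57.7% |
| 25% | 43.5 | 39.9% | 34.8 | 33.1% |

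For 80% power the formula needs (1.96 + 0.8416)² × 15 = 117.7, or 118 per arm. That is 118/174 = 68% of the 348 before attrition, or 118/139.2 = 85% after it. No share reaches 95%.

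**Fit with the other phases.** 348/87 = 4 patients per hospital over all five phases. The hospital criterion in section 2.1.1 reads "Hospitals should have at least 100 patients with influenza diagnosed by laboratory testing between 2021 and 2023", which implies at least 87 × 100 = 8,700 laboratory-diagnosed cases. This measures hospital volume before patient consent and exclusions and is not a planned analysis count, but it is of a different order from 348. Neither the model-development records nor the Phase V admissions fit inside a total of 348.

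**The case against.** The strongest reply is that this is one badly worded sentence. The sponsor may have meant 348 for Phase IV alone, with the retrospective records and Phase V admissions on top, in which case no power is lost through the allocation. That is plausible, and the documents do not rule it out. It explains the error without removing it, because section 2.5.3 still says something else.

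A second reply is that section 2.5.1 names no phase, and that Phase II, which is retrospective, also compares clinicians with and without the model on AUC. The link from 348 to Phase IV is therefore an inference. It is a strong one: section 2.3.4 names the between-group AUC difference as the Phase IV primary outcome and uses the same 0.15 threshold. If 348 was meant for Phase II, the randomised phase would have no stated patient number at all.

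Two stronger readings are tempting and are not supported:

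- A reader might infer that Phase IV has 87 per arm and 67% power instead of 95%. The half split is only one row of the table. At a 90% share, power stays above 80% even after 20% loss. Nor is 95% the right baseline, because the full 174 per arm gives only 92.6%, or 86.1% after loss.
- A reader might infer that the deep network is trained on a few hundred patients or fewer. Section 2.3.1 applies its 80/20 split to the collected records and never ties that pool to the 348.

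**Conclusion.** The contradiction between sections 2.5.2, 2.5.3 and 2.7.2 stands and must be resolved, because it concerns the patient number for the primary comparison. Any non-zero retrospective share leaves Phase IV below 174 per group. How far below cannot be determined. Over shares from 100% down to 25%, power runs from 92.6% to 39.9%, or from 86.1% to 33.1% after 20% loss. Once attrition is allowed for, the weaker target in section 2.5.4 holds only if about 85% or more of the 348 are in Phase IV.

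These figures assume that 348 was meant for Phase IV. They also take the plan's formula at face value, with equal arms and patients treated as independent although clinicians are the randomised unit. The documents do not establish that Phase IV will in fact be severely underpowered. They establish that the stated total cannot be both the two-arm requirement and the study-wide enrolment.

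**What to change.** In section 2.5.3, delete the statement that the 348 comprise both retrospective and prospective cohorts. State the Phase IV number per arm as prospective patients only, none of them used in model training or tuning. Report the retrospective Phase I and II records, and the Phase III and Phase V patients, separately from that number.

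Do not carry 174 forward unchecked. Choose one of two routes and bring the power targets in sections 2.5.1 and 2.5.4 into line with it:

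- Keep 95% power. This needs 195 per group before attrition, which becomes 234 by the plan's multiplication (195 × 1.2) or 244 by division (195/0.8). The totals are 468 or 488.
- Keep 174 per arm and state what it delivers by the plan's formula: 92.6%, or 86.1% after 20% loss.

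If 348 was always intended for Phase IV, keeping 174 costs only wording, since the retrospective records and Phase V admissions are already planned. If 348 was the real recruitment ceiling for the whole study, Phase IV needs additional prospective patients, and the sponsor should say so. Keeping 95% power also requires more Phase IV patients than 348.
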